## Abstract

**Background:**

Neuroblastoma, one of the most common extracranial solid tumors in children, often results in significant functional impairments, including muscle atrophy, reduced motor function, and sensory disturbances. While aerobic exercise has been shown to support functional recovery in patients with cancer, digital therapy–based aerobic exercise interventions have not yet been explored in pediatric neuroblastoma.

**Objective:**

This study aims to develop and evaluate a digital intervention therapy to provide a safe, feasible, and tolerable home-based physical activity initiation protocol for children with neuroblastoma after chemoradiotherapy, with the main objectives of (1) breaking sedentary behavior habits and increasing daily energy expenditure, (2) gradually improving physical function (flexibility, basic muscle strength and muscle endurance, and balance ability), (3) establishing the habit of regular exercise and improving exercise self-efficacy, and (4) laying the foundation for a possible transition to more standard, albeit low-risk, aerobic exercise.

**Methods:**

A total of 68 participants will be recruited and allocated to 2 groups matched in age and gender, with consideration given to the preferences of participants and their guardians. The control group will receive standard in-hospital medical treatment and health education, whereas the experimental group will receive a 6-month digital therapy–based aerobic exercise intervention in addition to standard care. Outcomes will be assessed at baseline and 3 and 6 months, with data collected for analysis. The primary outcomes are the 6-minute walk distance and the timed scores (in seconds) for the timed up and go and stair climb tests. The secondary outcomes include body composition, grip strength, and quality of life measured using the Pediatric Quality of Life Inventory version 4.0.

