### Participants

Children aged 6 to 17 years with a confirmed diagnosis of neuroblastoma will be recruited from outpatient clinics at the research center. Participants will be recruited based on inclusion and exclusion criteria.

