### Grouping and Masking

Participants with a clear preference for either intervention will be allocated accordingly, whereas those without a preference will be randomly assigned to the experimental or control group. This approach was adopted to accommodate the preferences of the participants and their guardians while preserving the benefits of randomization. Due to the nature of the intervention, participants and intervention providers will not be blinded to group allocation. However, outcome assessors and statisticians will remain blinded to group assignments to minimize bias.

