### Statistical Analysis

Data will be analyzed using SPSS (version 26.0; IBM Corp). Primary models using the intention-to-treat principle will be conducted for all primary and secondary outcomes. Data normality will be assessed initially. Nonnormally distributed data will be presented as medians with IQRs. Between-group comparisons (intervention vs control) for these variables will be conducted using the Mann-Whitney *U* test. Within-group comparisons (baseline vs each follow-up) will be conducted using the Wilcoxon signed rank test. Categorical data will be reported as numbers with percentages and analyzed using the chi-square test. Differences in primary and secondary outcomes between the intervention and control groups across all assessment time points will be evaluated using mixed-model analysis. Statistical significance will be defined as a *P* value of <.05, with multiple comparisons adjusted using the Bonferroni method.

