### Limitations

Despite its potential, this study has several limitations that should be considered when interpreting the results. First, the single-center design and small sample size restrict the generalizability of the findings. Future research should involve multiple centers across different regions and include larger samples to enhance external validity. Second, although outcome assessors and statisticians were blinded, participants and care providers were not. Furthermore, for participants with a preexisting preference, allocation was based on that preference rather than randomization. This nonrandomized allocation for a subset of participants introduces potential performance and expectation biases. As a preliminary investigation, this study provides foundational insights that can inform the design of a more rigorous randomized controlled trial in the future. Finally, the digital therapy platform and exercise programs are self-developed, and no formal large-scale usability testing was conducted before the intervention. While the design was informed by pediatric expertise and in-study engagement metrics supported feasibility, future iterations would benefit from structured usability testing to optimize the platform before broader implementation.

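### The abstract presents the two groups as matched on age and gender, but the stated allocation rule has no step that assures this, and allocation by preference is incompatible with assuring it

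*Protocol article*

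**What the plan says.** The Methods paragraph of the abstract gives matching as a property of the design: "A total of 68 participants will be recruited and allocated to 2 groups matched in age and gender". The same sentence adds that the preferences of participants and guardians are taken into account.

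Grouping and Masking gives the rule in two parts. For the first group of children, "Participants with a clear preference for either intervention will be allocated accordingly"; for the rest, "those without a preference will be randomly assigned to the experimental or control group". No matching, stratification or minimisation factor is named.

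Limitations returns to allocation and says that "for participants with a preexisting preference, allocation was based on that preference rather than randomization". It names performance and expectation biases as the consequence and does not mention age or sex.

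The population is broad: "Children aged 6 to 17 years with a confirmed diagnosis of neuroblastoma will be recruited". On analysis, the article says "Differences in primary and secondary outcomes between the intervention and control groups across all assessment time points will be evaluated using mixed-model analysis".

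**The concern.** The abstract tells the reader that the arms are comparable on age and gender. The rule that a site would apply does not assure that. This is more than a detail left out of a condensed article: one section asserts a property, and another gives a rule covering every child that does not deliver it.

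The primary outcomes are walking distance and timed mobility tests, and the secondary outcomes include grip strength and body composition. In children from 6 to 17 years these plausibly vary with age and sex. If older children or their families lean towards one arm, the groups will differ for a reason unrelated to the intervention. A reader who takes the abstract at its word would not look for that.

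**Working it through.** **1. The sections side by side.**

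| Section | What it says about matching |
|---|---|
| Abstract, Methods | Groups are matched on age and gender |
| Study Design | Nothing |
| Participants | Age range only |
| Grouping and Masking | Two routes, preference or random; no matching step |
| Statistical Analysis | Mann-Whitney test and a mixed model; no matched term named |
| Sample Size Calculation | Two-group calculation; no matching |
| Limitations | Preference allocation acknowledged; matching not mentioned |

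Each child either has a clear preference or does not, so the two routes cover everyone. On the preference route, age and sex play no part in the assignment, so matching cannot be assured there. On the random route, stratification would be possible but is not stated.

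**2. The plan's own figure.** The inputs come from Sample Size Calculation: means 35.89 and 26.76 laps, SDs 8.46 and 10.57, alpha .05, power 0.95.

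- Effect size: (35.89 − 26.76) / √((8.46² + 10.57²)/2) = 9.13 / 9.57 = 0.954, against 0.953 stated.
- A two-sided independent-samples t test with d = 0.953 needs 30 per group (power 0.952).
- Dropout: 30 / (1 − 0.10) = 33.3, rounded up to 34 per group, 68 in total.

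The figures reproduce as an unmatched comparison, so correcting the matching claim changes none of them.

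**3. Chance imbalance in age.** The article gives no age distribution. Assume whole-year ages spread evenly over 6 to 17 (12 values) and all 34 per arm randomised without stratification.

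- SD of age = √((12² − 1)/12) = 3.45 years.
- SE of the difference in mean age = 3.45 × √(2/34) = 0.84 year.
- 95% range = ±1.96 × 0.84 = about ±1.6 years.
- Simulated probability of a difference above 1 year: 0.227, or about 23%. Above 2 years: 0.016.

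These figures depend on the assumed distribution; ages clustered more tightly would make them smaller.

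**4. Systematic imbalance through preference.** Let f be the share of children with a preference (taken as equal in the two arms) and g the mean-age gap between those preferring one arm and those preferring the other. Children without a preference have the same expected age in both arms, so the expected difference is f × g. The article gives neither quantity. Over assumed ranges:

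| f | g = 1 year | g = 2 years | g = 3 years |
|---|---|---|---|
| 25% | 0.25 | 0.50 | 0.75 |
| 50% | 0.50 | 1.00 | 1.50 |
| 75% | 0.75 | 1.50 | 2.25 |

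The two sources differ in kind. Chance imbalance under randomisation is already allowed for in the standard error and P value. A shift produced by preference is not.

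**The case against.** The strongest reply is that the article condenses a fuller protocol. Random assignment is compatible with stratification, and covariates are commonly left to a statistical analysis plan. That stands for the random route, and it means that the absence of age and sex from the model sentence is not an error in itself. It does not rescue the matching claim, because stratifying the random list would still leave the children placed by preference unmatched.

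A second reply is that Limitations already discloses the nonrandomised allocation. It does, but it does not correct the abstract's claim about age and gender.

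A reader might also infer more than the documents support:

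- *That matching was promised as protection against growth and development effects.* No section gives matching a purpose.
- *That the rule makes comparable groups impossible.* It does not assure them; they could still arise.
- *That an age difference translates directly into a biased walking-distance effect.* The mixed model covers all assessment times, baseline included. A group-by-time contrast would largely remove a constant difference in level, leaving only differences in change related to age or sex. The article gives nothing from which to size these.
- *That imbalance should be judged in the randomised children alone.* The planned comparison is by intention to treat in all 68.

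**Conclusion.** The point holds as an internal contradiction: the abstract claims a property that the described allocation does not assure and that its preference route cannot assure. Its size can be shown only under assumptions. Chance alone would give a mean-age difference above 1 year about 23% of the time with uniform ages and 34 randomised per arm. Preference could add an expected 0.25 to 2.25 years over shares of 25% to 75% and gaps of 1 to 3 years. Sex imbalance is not quantified. No bias in any outcome is demonstrated. What is established is a misstatement about comparability in a partly nonrandomised trial, and one that is cheap to correct.

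**What to change.** - **Abstract.** Delete the matching claim. State that allocation is by preference or, where there is none, by randomisation.
- **Statistical Analysis.** Name age, sex and the baseline value of the outcome as fixed covariates in the mixed model for all 68 children. If the baseline value is a covariate, the 3- and 6-month values are the responses, and the model sentence should say so.
- **Optional.** Stratify the random list for children without a preference by age band and sex, without claiming that this balances the children allocated by preference.

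The cost is small. Demographic information is recorded at baseline in both groups, and the study timeline schedules the outcomes at visit 0, so no new data are needed. Adjustment reduces confounding by the named factors only; it does not make the preference comparison equivalent to a randomised one. Optional stratification has a real drawback: strata would be sparse in a randomised subset of unknown size, and small blocks at a single centre with unblinded intervention providers would make upcoming assignments easier to predict. The planned numbers per group and in total stay as they are.

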**Results:**

Recruitment will be conducted from December 2025 to September 2026. We expect that the intervention group will show significantly greater improvements in physical function, physical activity levels, and fatigue management than the control group, demonstrating the effectiveness of digital therapy for rehabilitation training after radiotherapy and chemotherapy for neuroblastoma in children.

**Conclusions:**

We expect that the results of this study will provide evidence for rehabilitation after chemoradiotherapy in pediatric patients with neuroblastoma to improve physical function, physical activity levels, and fatigue management. In the future, expanding to multiple centers to conduct targeted surveys of different types of childhood cancers will help validate the effectiveness of digital therapy.

**International Registered Report Identifier (IRRID):**

DERR1-10.2196/72698

## Introduction

Neuroblastoma is one of the most common solid tumors in children, accounting for 8% to 10% of all childhood cancers, with a global incidence of approximately 10.1 cases per million children annually [1,2]. The clinical presentation of neuroblastoma varies depending on the tumor’s location and severity, often involving compression or invasion of neural structures. Standard treatments such as radiotherapy, chemotherapy, immunotherapy, and surgery can lead to adverse effects, including fatigue, vomiting, and malnutrition [3,4]. Additionally, children with neuroblastoma frequently experience limb motor dysfunction (eg, hypokinesia), sensory deficits, behavioral and cognitive impairments (eg, learning difficulties and attention-deficit/hyperactivity disorder), mood disorders, and sleep disturbances [5,6]. Given that childhood is a critical period for physical and mental development, the long-term impact of neuroblastoma on cardiopulmonary fitness and quality of life underscores the importance of early exercise interventions [7].

There is a growing body of preclinical evidence suggesting that exercise positively influences the tumor microenvironment, enhances immune function, and supports nervous system health [8,9]. In clinical settings, exercise has been shown to accelerate postoperative recovery, improve physical activity levels and cardiopulmonary fitness, and alleviate cancer-related fatigue in patients undergoing radiation or chemotherapy [10]. Combined exercise interventions alongside chemotherapy and surgery have been reported to reduce tumor growth rates by 31% to 67% and lower the risk of metastasis [11]. Furthermore, preoperative exercise interventions may decrease postoperative complications and shorten hospital stays [12]. Braam et al [13] demonstrated that exercise interventions during and after cancer treatment improve body composition, flexibility, cardiorespiratory fitness, muscle strength, and quality of life in pediatric patients with cancer. A systematic review of exercise interventions in children with acute lymphoblastic leukemia highlighted their benefits in reducing fatigue during chemotherapy and maintaining physical activity, muscle strength, bone density, and functional capacity after treatment [14].

Aerobic exercise, the most commonly studied form of exercise intervention in oncology, has been shown to enhance cardiovascular fitness, boost metabolism, strengthen muscles, improve quality of life, reduce fatigue, and alleviate depression [15-17]. For instance, Leclerc et al [18] reported significant improvements in motor function, body fat percentage, and quality of life in patients with breast cancer following a 3-month multidisciplinary aerobic exercise program. Similarly, Tanriverdi et al [19] found that a virtual reality–based aerobic exercise intervention improved sleep quality in children with acute lymphoblastic leukemia. Despite these benefits, patient adherence remains a significant barrier to the implementation of exercise interventions. Blanchard et al [20] noted that 52.7% to 70.4% of patients with cancer in the United States fail to meet recommended exercise guidelines. Strategies to enhance adherence and intervention efficacy are critical for advancing this field. For example, Le et al [21] demonstrated that a 12-week telephone-based exercise intervention improved physical activity, fatigue, quality of life, and vitality in survivors of cancer. However, such interventions require substantial manpower and lack direct interaction, highlighting the need for more scalable and interactive solutions.

The integration of digital health technologies into health care services has opened up new avenues for innovation. Digital therapeutics (DTx), which use evidence-based software programs to deliver interventions for disease treatment, management, or prevention, represent a promising approach [22]. DTx leverage artificial intelligence to enable effective disease monitoring, provide personalized treatment plans, and enhance health care delivery [23]. In 2019, the World Health Organization endorsed digital rehabilitation as a continuous care model in its guidelines on digital interventions for health system strengthening [24]. DTx for aerobic exercise interventions are now widely used in managing chronic conditions such as heart disease, diabetes, and obesity [25]. Studies have shown that users of digital platforms are more likely to achieve exercise-related benefits compared to nonusers [26], and DTx have demonstrated high engagement and acceptability among children and their parents [27]. Compared with traditional face-to-face aerobic training, DTx-based aerobic exercise offers several distinctive advantages, including real-time feedback, science popularization and patient education, and adaptive intensity adjustment through data analytics. These features contribute to higher user motivation, better adherence, and more precise monitoring of exercise quality and safety [28,29]. By transcending time and space limitations, DTx enable real-time remote guidance, intervention quality monitoring, and reduced hospitalization frequency, thereby improving intervention efficiency and alleviating the burden on health care providers.

While animal studies have demonstrated the positive effects of exercise on physical function, immunity, and tumor prognosis in neuroblastoma models [30], clinical evidence on the impact of DTx-based aerobic exercise in children with neuroblastoma remains scarce. This study aims to address this gap by investigating the effects of a novel aerobic exercise–based digital therapy intervention on motor function and quality of life in children with neuroblastoma.

## Methods

### Study Design

This study is a single-center, prospective clinical trial designed to evaluate the efficacy of a digital therapy–based aerobic exercise intervention in children with neuroblastoma. The trial adheres to US Food and Drug Administration certification and management standards for digital therapy. Participants will be divided into 2 groups: the control group will receive routine in-hospital diagnosis and treatment, whereas the experimental group will receive a digital therapy–based aerobic exercise intervention in addition to standard care. Following group allocation, the control group will receive physical activity guidance from clinicians as part of conventional care, whereas the experimental group will follow a personalized digital exercise management program tailored to their disease condition and lifestyle (Figure 1). The trial aims to establish a digital management model for children with neuroblastoma through statistical analysis of clinical outcomes.

**Figure 1 figure1:**
[figure not shown]
Digital management pathway for children with neuroblastoma. 6MWD: 6-minute walk distance; PedsQL 4.0: Pediatric Quality of Life Inventory version 4.0; WHO: World Health Organization.

### Participants

Children aged 6 to 17 years with a confirmed diagnosis of neuroblastoma will be recruited from outpatient clinics at the research center. Participants will be recruited based on inclusion and exclusion criteria.

### Inclusion Criteria

The inclusion criteria are as follows: (1) confirmed diagnosis of neuroblastoma requiring radiotherapy or chemotherapy, (2) age of 6 to 17 years, (3) ability to understand and express themselves to some degree, (4) ability of the patient or their guardian to operate a smartphone app, (5) awareness of the patient’s condition and prognosis by the patient or their guardian, and (6) voluntary participation with signed informed consent from the patient and their guardian.

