### Exclusion Criteria

The exclusion criteria are as follows: (1) preexisting malignant tumors or other types of solid or nonsolid tumors; (2) disease progression or recurrence at the time of study enrollment; (3) heart rate (HR) exceeding 70% of the age-specific maximum or below 60 beats per minute, systolic blood pressure of >180 mm Hg or orthostatic hypotension, respiratory rate of >50 breaths per minute, body temperature of >37.5 °C, or oxygen saturation of <90%; (4) occurrence within 3 months before enrollment of cardiac insufficiency (New York Heart Association functional class II or higher), severe pulmonary function decline, fracture, hypertension of grade ≥2, or concurrent use of ≥2 antihypertensive medications; (5) history of HIV infection, active hepatitis B virus or hepatitis C virus infection, or uncontrolled systemic infection; and (6) major surgery within 4 weeks before enrollment or planned major surgery during the study period.

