### Withdrawal Criteria

Participants will be withdrawn from the study for the following reasons: (1) serious violation of the test protocol by the participant or their guardian or (2) receipt of other treatments by the participants during the trial that interfere with the study.

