## Results

Recruitment will be conducted from December 2025 to September 2026. It is expected that the intervention group will show significantly greater improvements in physical function, physical activity levels, and fatigue management compared to the control group and that the effectiveness of digital therapy for rehabilitation training after radiotherapy and chemotherapy for neuroblastoma in children can be demonstrated. The findings of this study are anticipated to be published by late 2026 or early 2027.

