### Conclusions

This study represents an important first step in aerobic digital therapy for pediatric neuroblastoma. It provides evidence that rehabilitation after chemoradiotherapy in pediatric patients with neuroblastoma can improve physical function, physical activity levels, and fatigue management. In the future, expanding to multiple centers to conduct targeted surveys of different types of childhood cancers will help validate the effectiveness of digital therapy–based aerobic exercise.

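### The eligibility criteria do not ensure the post-chemoradiotherapy population that the objective, expected results and conclusions name

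*Protocol article*

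**What the plan says.** Two descriptions of the population stand in the Protocol article.

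- **After treatment.** The abstract's Objective describes a "home-based physical activity initiation protocol for children with neuroblastoma after chemoradiotherapy". The Results section expects to show the "effectiveness of digital therapy for rehabilitation training after radiotherapy and chemotherapy for neuroblastoma in children", and the abstract's Results match it. The closing Conclusions state: "It provides evidence that rehabilitation after chemoradiotherapy in pediatric patients with neuroblastoma can improve physical function". The abstract's Conclusions are framed in the same way.
- **Neuroblastoma in general.** The aim at the end of the Introduction, the Study Design section and the primary objective under Expected Findings refer to children with neuroblastoma and mention no treatment phase.

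Eligibility is set in three places. Inclusion criterion 1 asks for a "confirmed diagnosis of neuroblastoma requiring radiotherapy or chemotherapy". Under Participants, children "will be recruited from outpatient clinics at the research center". The Exclusion Criteria remove "disease progression or recurrence at the time of study enrollment" and "major surgery within 4 weeks before enrollment or planned major surgery during the study period", along with rules on vital signs, recent cardiac, pulmonary, fracture or blood pressure problems, infections and other tumours.

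Under Grouping and Masking, participants with a clear preference go to the arm they prefer, and only those without one are randomised.

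**The concern.** The claims and the criterion differ in timing (after treatment, against a disease that requires it) and in modality (both, against either). The criterion does not rule out a child whose treatment is pending or under way, or one who receives a single modality.

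Two things are at stake. First, a reader of the final report would be told about rehabilitation after chemoradiotherapy from a sample not defined in that way. Second, the Introduction itself lists fatigue, vomiting and malnutrition among the effects of standard treatment, so treatment phase plausibly affects walking distance, the timed tests and quality of life. Where arms are formed partly by preference, randomisation does not balance phase across the whole sample. The abstract mentions matching on age and gender only.

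**Working it through.** **Plan's own figure.** The sample size reproduces, and the point does not depend on it. From the means and SDs under Sample Size Calculation, d = (35.89 − 26.76) / √((8.46² + 10.57²)/2) = 9.13 / 9.573 = 0.954, against 0.953 stated. A two-sided 5% t test at 95% power needs 29.6, so 30 per arm. Allowing for 10% loss, 30 / 0.9 = 33.3, so 34 per arm and 68 in total.

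**Does any eligibility rule close the gap?**

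| Rule | Requires radiotherapy or chemotherapy to be finished? |
|---|---|
| Inclusion criterion 1 | No. It names a need for treatment, and either modality suffices |
| Outpatient recruitment | No. It fixes the setting, not the phase |
| Exclusion for progression or recurrence | No. It concerns disease status |
| Exclusion for major surgery | No. It sets a 4-week window for surgery; radiotherapy and chemotherapy have no counterpart |
| Remaining exclusions | No. They concern vital signs, recent medical events, infections and other tumours |

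None does. The surgery window shows that treatment timing was specified where the authors wanted it.

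**Illustration of bias from unequal phase.** The documents give neither the effect of phase on any outcome nor the mix of phases, so both inputs below are assumptions. Let D be the difference in mean outcome between phases, in SD units, and p the difference between arms in the proportion on treatment. With no true effect the arms differ by D × p, and the t test with n = 30 per arm has noncentrality D × p × √(n/2) = D × p × 3.873 on 58 degrees of freedom.

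| D (SD) | p | Shift (SD) | False rejection, two-sided 5% |
|---|---|---|---|
| 0.3 | 0.10 | 0.030 | about 5% |
| 0.5 | 0.25 | 0.125 | 7.6% |
| 1.0 | 0.25 | 0.250 | 15.9% |

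Two refinements lower the last row:

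- If 1 SD is the within-phase SD and the arms are 50% and 25% on treatment, the variances become 1 + 0.5 × 0.5 = 1.25 and 1 + 0.25 × 0.75 = 1.1875. Their mean is 1.219, the standardised shift is 0.25 / 1.104 = 0.226, and the rate is 13.9%.
- If Bonferroni is applied over the three primary outcomes (0.05 / 3 per test), the rate for the 0.25 SD shift is 7.4% per test.

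These rates are for an unadjusted comparison at one follow-up visit. The plan states a mixed model over all time points. A phase difference that is stable from baseline would not by itself appear as a group-by-time effect; different recovery by phase could.

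**The case against.** The strongest reply is that this is a conflict of wording. Three sections use the broader description, and the criterion fits them. The verb in criterion 1 can also be read as describing children whose disease called for treatment, which would suit a post-treatment sample. In practice the children enrolled may all have finished treatment. The Limitations section already concedes bias from preference allocation, disease information is already taken from hospital records, and covariate choice is often left to the analysis plan.

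Much of this stands, and it limits what can be said. Three stronger readings are tempting and are not supported:

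- **That the enrolled population will not match the conclusion, or that every phase is plainly eligible.** The wording is ambiguous. On a present-tense reading a child years past treatment is not clearly eligible. The documents show only that the criteria do not ensure the stated population.
- **That the withdrawal rule would remove children for therapy that the inclusion rule expects.** That rule concerns "receipt of other treatments by the participants during the trial that interfere with the study". Both arms receive standard care by design, so the natural reading is treatment outside that care. Radiotherapy and chemotherapy are not named.
- **That the false-positive rate is 16%.** That is the top of an assumed range, and it leaves out the planned baseline measurement and multiplicity adjustment. Nothing in the documents shows that families of children on treatment would avoid the exercise arm.

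The reply does not remove the conflict itself. The article prints its list of criteria and its conclusions, and they describe different populations. A fuller document would not reconcile those published statements.

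**Conclusion.** The point holds in limited form. The criteria leave pending treatment, ongoing treatment and single-modality treatment open, while the objective, expected results and conclusions are worded for children after chemoradiotherapy. This rests on the text alone and needs no numerical assumption.

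The consequence for bias is possible but unquantified. For phase differences of 0.3 to 1 SD and imbalances of 10 to 25 percentage points, false rejection runs from about 5% to 16% in an unadjusted test, and lower with baseline adjustment or Bonferroni. These figures illustrate the risk; they do not estimate it. The correction should be made because it is cheap and decides whom the result applies to.

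**What to change.** The sponsor should state which population is intended and reconcile the text by one of two routes:

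1. make inclusion criterion 1 require completed treatment, naming the modality or modalities meant; or
2. restate the objective, expected results and conclusions for the population that the criterion admits.

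The general descriptions in the Introduction, Study Design and Expected Findings should then agree with the choice. Which population is right is for the sponsor to decide.

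If more than one treatment phase is admitted, take phase and time since last treatment from the hospital records at baseline in both arms, and include phase as a covariate in the mixed model.

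The cost is a sentence or two of text and, unless already collected, two baseline items from a source already in use. Tightening the criterion may slow recruitment slightly. Recruitment is planned from December 2025 to September 2026, so the sooner this is settled, the fewer children enter under an ambiguous rule.
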